## Blinding

This is a double blinded study. Both the study staff and the caregivers are blinded to which intervention is allocated to the study participant. Products are designed to be as indistinguishable as possible. The reference group is aware that they are not allocated to an intervention, however, the clinical study staff will not be made aware of which group participants are allocated to.

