### Random allocation

Thereafter, caregivers are informed of allocation to supplementation or the reference group. Those not allocated to supplementation are given a token of appreciation (given at each follow-up clinic visit), valued at around 5000 UGX but not more than 10 000UGX, for example clothes soap. If allocated to LNS caregivers are given training concerning appropriate use of LNS before they are allocated a two week supply. Prior to departure all caregivers are given a follow-up plan. Refer to the SOP for further details.

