### Follow-up clinic visits

All caregivers and study participants are requested to return to a specific study site for a follow-up visit at 2, 4, 8 and 12 weeks post inclusion. Those receiving LNS are also requested to return at 6 and 10 weeks post inclusion to restock sachets.

At follow-up clinics child anthropometrics are measured, a clinical review is done and inquiries are made into LNS compliance (if relevant). At week 12, additional parameters are measured; blood and stool samples are collected and bioimpedance and child development are assessed and a discharge questionnaire is completed. An overview of the measurements taken at each time point are provided in figure 4.

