# Strategies to improve and monitor adherence

It is a challenge to ensure that the participating child is the one receiving the LNS, due to home based caregiver administration. As such, several actions are taken to improve compliance.

- Siblings: We aim to only include one child per household in the study. However, if there are other young children in the household (6 months to five years), instructions and sachets will be given so that the caregiver receives extra rationing. This strategy aims to minimize the likelihood of sharing.
- Identification: Several methods are used to ensure that the correct child is matched to the correct study records, namely wrist bands and photo id. The SOP describes the use of these processes in detail.
- Accountability: Any distribution of sachet stocks will be logged by study staff. Additionally, when collecting new sachets, the caregiver is requested to return the empty sachets from their previous two week supply. This is to improve accountability on the part off the caregivers, and encourage against sachet redistribution or selling.
- Monitoring adherence: Trained study staff will make regular phone follow-up calls to the participant/caretakers to remind them of their clinic visits and enquire about stool sample collection or LNS adherence where applicable. At clinic visits and when the caregiver is collecting sachet stocks study staff will also enquire about LNS adherence.
- Incentives: Throughout the study, the child’s health will be monitored regularly. A travel reimbursement of not more than 20,000UGX will be provided to cover the cost of return transport and includes some allowance for e.g. food purchase during the day while at the clinic visit. Any caregivers attending with unsupplemented children will also receive a small token which can be appreciated by the whole family, for example clothes soap. The value will not exceed 10,000UGX.

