## Product distribution

Product distribution takes place away from other study operations. The product distributor/s are solely responsible for product distribution and product monitoring at each site. They will not be involved in any clinic related data collection. In the interest of compliance, caregivers are requested to return empty sachets to the product distributor at each visit. The distributor keeps a confidential supplement distribution log.

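### Clinic staff are promised to be unaware of group, yet compliance questions and a reference-only token at the measurement visits can show them who receives LNS

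*Protocol*

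**What the plan says.** The Blinding section makes two statements. The first is general: "Both the study staff and the caregivers are blinded to which intervention is allocated to the study participant". The second follows directly on the admission that reference families know they receive no product: "the clinical study staff will not be made aware of which group participants are allocated to". Because of where it stands, the second statement covers LNS v no LNS, and not only which of the four products a child receives.

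Three other sections describe what happens at visits:

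- Follow-up clinic visits: "At follow-up clinics child anthropometrics are measured, a clinical review is done and inquiries are made into LNS compliance (if relevant".
- Strategies to improve and monitor adherence: "At clinic visits and when the caregiver is collecting sachet stocks study staff will also enquire about LNS adherence".
- Random allocation: "Those not allocated to supplementation are given a token of appreciation (given at each follow-up clinic visit". The adherence section repeats the arrangement: "Any caregivers attending with unsupplemented children will also receive a small token which can be appreciated by the whole family, for example clothes soap".

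The Product distribution section holds the relevant safeguard. Distribution is kept apart from other operations, and of the distributors it says: "They will not be involved in any clinic related data collection". Allocation sequence concealment makes distribution staff the only study personnel with access to the allocation sequence.

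**The concern.** A question put only to families for whom it is relevant requires the asker to know, or to find out, whether the child is on LNS. A token given only to reference families carries the same information. Both occur at visits where the child is measured.

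Caregivers on both sides of the LNS v no LNS contrast know their status, so masking of those who assess the child is the main protection against observer bias there. Knee-heel length, length, skinfolds and MUAC are read by a person, and the MDAT is scored by one. If an assessor knows that a child is unsupplemented, readings may drift in one direction. The analysis could not separate that drift from an effect of supplementation.

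**Working it through.** **Setting the sections side by side**

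1. Blinding: clinical staff are not to know the group, reference group included.
2. Follow-up clinic visits: anthropometry, clinical review and compliance questions are listed together for the same clinic.
3. Adherence section: clinic visits and sachet collection are named as two occasions for asking. The question is therefore not confined to the distribution point.
4. Random allocation: the token goes to one side of the contrast only, at each follow-up clinic visit. No giver and no place are stated.
5. Product distribution: the distributors are separate, but neither the compliance questions nor the token is assigned to them.
6. Further cues: only LNS families are called back at weeks 6 and 10, and Phone call follow-up puts LNS compliance in the same call as medical history and adverse events.
7. No section asks caregivers to keep their group to themselves, or states that those who measure are kept away from items 3, 4 and 6.

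Items 2 to 4, followed as written, expose LNS v no LNS status to clinic staff. That conflicts with item 1, and item 5 does not resolve it.

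**The protocol's own figure**

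Inputs from Sample size: 5% significance (taken as two-sided), 80% power, 600 v 150, 10% loss, SD of baseline knee-heel length 18.1 mm.

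- Numbers after loss: 600 × 0.9 = 540 and 150 × 0.9 = 135.
- SE in SD units = √(1/540 + 1/135) = 0.0962.
- Detectable difference = (1.960 + 0.842) × 0.0962 = 0.270 SD.
- In millimetres, 0.27 × 18.1 = 4.89.

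The stated 0.27 SD and 4.9 mm are reproduced.

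**What an observer shift would mean**

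The documents give no observer shift and no SD for 12-week growth. Both are assumed here: a shift of 0.5 mm and a growth SD of 2 to 5 mm.

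| SD used | 0.27 SD in mm | 0.5 mm as a share |
|---|---|---|
| 18.1 mm (protocol, baseline length) | 0.27 × 18.1 = 4.89 | 0.5/4.89 = 10% |
| 5 mm (assumed, growth) | 0.27 × 5 = 1.35 | 0.5/1.35 = 37% |
| 2 mm (assumed, growth) | 0.27 × 2 = 0.54 | 0.5/0.54 = 93% |

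A second illustration takes no true effect and a shift of b SD between supplemented and reference children. The two-sided type I error is 1 − Φ(1.960 − b/0.0962) + Φ(−1.960 − b/0.0962). For b = 0.05, 0.10 and 0.15 it is about 8%, 18% and 34%, against a nominal 5%. On the 18.1 mm SD these shifts are 0.9, 1.8 and 2.7 mm. On an assumed growth SD of 5 mm, 0.10 SD is 0.5 mm.

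**The case against.** The strongest reply is that nothing in the protocol places the compliance question or the token in the measurer's hands. The sections put them at the same clinic, not with the same person. Several staff roles are listed, the development test is given to staff trained for it, and distribution is already separated. The site-flow figure is not available here and detail is left to the SOP, so the order of stations may already protect the measurers. This stands: a reader might infer that measurers will be unmasked, and the text does not support that. It does support that clinic staff other than the distributors can learn LNS status, which the Blinding section says they will not.

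Second, a reader might infer that the primary comparison is compromised. It is not. All 600 children in the 2x2 comparison are on LNS, are asked the same questions and receive no token, and the four products are hidden behind eight codes. The cues do not distinguish one product from another. The protocol calls the 600 v 150 comparison secondary.

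Third, some protection exists apart from masking: a digital knemometer, repeated measurements, trained staff and calibrated equipment. These narrow the room for drift but do not remove it. Haemoglobin and the laboratory markers are much less exposed.

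Fourth, the upper shares in the table depend entirely on the assumed growth SD. Against the protocol's own 4.9 mm, a 0.5 mm shift is small. That also stands, and the larger shares should not be read as an estimate of bias.

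**Conclusion.** The conflict is real and lies in the text. The promise that clinical staff will not know the group cannot be squared with clinic-visit compliance questions put only to LNS families and a token given only to reference families at follow-up visits. Whether those who measure are affected is left open.

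The consequence is limited to the secondary 600 v 150 comparison, and there to observer-read outcomes: knee-heel length, length, skinfolds, MUAC and MDAT.

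The size of any bias cannot be derived from the documents. With an assumed 0.5 mm shift it runs from about 10% of the detectable difference on the protocol's SD to 37–93% on an assumed growth SD of 5 to 2 mm. The finding rests on the contradiction and not on these figures. It is worth correcting because the remedy is cheap and an observer shift cannot be removed at analysis.

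**What to change.** In Random allocation, Follow-up clinic visits and Strategies to improve and monitor adherence:

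- Assign the clinic-visit LNS compliance questions and the token to the product distributors, at the separate distribution point.
- State that this happens only after anthropometry, clinical review and, where scheduled, the MDAT are finished.
- Ask caregivers not to mention their group or show the product before then.

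In Phone call follow-up, state that compliance questions are asked by staff who take no clinic measurements. The calls also cover health information, so there is no need to pass them to the distributors.

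If this is not adopted, restrict the staff-blinding statement to the four LNS products and report the 600 v 150 comparison as not securely assessor-masked.

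The cost is a small change to site flow and the SOP. The distributors already log sachets and collect empties, so the clinic questions fit their role. The CRF and staffing plan are not available, so any effect on forms or staff numbers cannot be judged here.

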## Product codes

The four LNS-LQ products are each allocated two different product codes so that there are 8 product codes in total. The product code document, stating which product corresponds to which product codes, is prepared and placed in sealed envelopes by Nutriset. These product codes are kept locked and will first be revealed following the primary analysis.

## Product distribution

Product distribution takes place away from other study operations. The product distributor/s are solely responsible for product distribution and product monitoring at each site. They will not be involved in any clinic related data collection. In the interest of compliance, caregivers are requested to return empty sachets to the product distributor at each visit. The distributor keeps a confidential supplement distribution log.

# Pilot phase

A pilot will be conducted prior to the study start. This is done in order to test the study procedures, CRFs and SOPs are operational and clear to all who will use them. During the pilot phase of the study, a maximum of 20 children will be enrolled. Study procedures will be carried out in order to test the protocol, questionnaires and staff roles. Importantly, there are two exceptions to following the protocol during the pilot: 1. No blood samples will be collected during the pilot phase and 2. Intervention products will not be used. Data collected during this period will be stored separately and will not be used as part of the study data.

# Data collection and measurements

## **A**ge and birth weight

In order to gather information on the child’s exact age and birth weight, caregivers are requested to provide a birth information card for that child. If this is not available, study staff will attempt to identify the child’s age through a series of questions.

## Sociodemographic and medical questionnaire

At baseline an interviewer-administered questionnaire is used to collect information on participant socio- demographic characteristics and medical history. A medical history questionnaire is also to be administered at 12 and 24 weeks.

## Clinical examination

A thorough physical examination is carried out at baseline including rapid tests for HIV and Malaria and assessment for vital signs (pulse, blood pressure and respiratory rate). At follow-up clinic visits thereafter, a short clinical review is conducted including information on recent medical history and milk consumption. If an illness is suspected, a treatment is recommended but not provided by the study. If necessary, the child is referred for treatment. Where relevant, the resolution/worsening of adverse events is monitored by clinic staff. The SOPs describe the process in further detail.

## Anthropometrics

Anthropometrics will be taken in repeated measures and on the left side of the body wherever possible. To reduce variation in the measurements, in as much as is possible, the same study staff will take anthropometric measurements, each having been specifically trained in anthropometrics. All equipment is calibrated regularly and the same equipment used (wherever possible) between study sites. All anthropometric measurements are feasible in the study context and are not invasive or harmful to participants.

### Child anthropometry

The following anthropometrics are taken at baseline, week 2, 4, 8 and 12 weeks; knee-heel length, MUAC, weight, height, skin folds (subscapular and triceps). The distance between the heel and knee is measured using a digital hand-held knemometer (Michaelsen KM et al, 1991). Knee-heel length is a sensitive measure of change in growth over short time periods, detecting smaller differences with less variation than overall height. Weight is measured using an electronic scale with a double weighing function. Height (measured in children 24 months and older) and length (measured in children <24 months) are taken using a standard wooden height/length board. The anthropometric indices HAZ, WAZ and WHZ are used to monitor nutritional status over time according to the WHO growth standards. Mid-upper-arm circumference is measured using a MUAC tape. A low MUAC has been associated with higher mortality risk in young children [29]. The MUAC has a high specificity and gives an indication of wasting and of lean mass accretion over time. Skin fold thickness is measured in the triceps and subscapular using a Harpenden skinfold caliper. Head circumference is measured using a non-stretch measuring tape at baseline, week 12 and week 24. Head circumference can be useful when interpreting child development outcomes.

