| **Measurable Outcomes:**  Primary outcome: Knee-heel length (mm) and total length (cm) over 12 weeks.  Secondary outcomes: HAZ, WAZ, WHZ, weight gain (g), body composition (bioimpedance and skin folds), head circumference, MUAC, haemoglobin (Hb) and child development, based on the Malawi Developmental Assessment Tool (MDAT) over 12 weeks.  Tertiary outcomes: Growth factors [Insulin-like growth factor-1 (IGF-1), insulin], markers of nutrient status [ferritin, soluble transferrin receptor (sTfR), vitamin B12, vitamin A and folate], markers of systemic inflammation, intestinal inflammation and intestinal function [C-reactive protein (CRP), alpha-1-acid glycoprotein (AGP), myeloperoxidase (MPO), neopterin (NEO), alpha-1-antitrypsin (AAT), citrulline], gut microbiota (diversity and composition), and morbidity over 12 weeks. | |
| **Study participants:**  750 children aged 12 -59 months with a HAZ <-2. | |
| **Study design:**  A randomised, double-blinded, community trial, testing four different large-quantity lipid-based nutrient supplements (LNS-LQ) in a two-by-two factorial design. A fifth un-supplemented group is included as a reference. Shown in figure 1. | |
| \|  \|  \| + Milk protein isolate (MPI) \|  \| + Soy protein Isolate (SPI) \| \| --- \| --- \| --- \| --- \| --- \| \| Whey permeate  (+ WP) \| A. \| LNS-LQ + MPI + WP  n=150 \| C. \| LNS-LQ + SPI + WP  n=150 \| \| No whey permeate  (-WP) \| B. \| LNS-LQ + MPI – WP  n=150 \| D. \| LNS-LQ + SPI - WP  n=150 \|  \|  \| Family diet \| \| --- \| --- \| \| E. \| Reference n=150 \|   **Figure 1:** Four large-quantity lipid-based nutrient supplements (LNS-LQ) in a two-by-two factorial design. Reference group continues with family diet. n= number of children allocated. MPI: Milk protein isolate, WP: whey permeate, SPI: soy protein isolate | |
| **Study site and recruitment:**  Study clinics are run from selected community health centres. Recruitment will take place in villages located nearby these selected community health centers | |
| **Participant inclusion:**  If both inclusion and exclusion criteria are fulfilled and informed consent is given, children are randomly allocated to one of four LNS-LQ or to an un-supplemented group. | |

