## Eligibility criteria

### Inclusion criteria

- Aged 12 - 59 months.
- HAZ <-2 (WHO growth standards).
- Care-taker able and willing to return for follow-up visits, an initial home visit and agrees to phone follow-up.
- Living within the catchment area.
- Written informed consent given by parent/caregiver.

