# Outcomes

All outcomes are measured over time from baseline to 12 weeks.

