## Primary outcome

- Knee-heel length (mm)
- Length/height velocity(cm)

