# Sample size

The sample size calculation is generic, based on the ability to detect differences in terms of standard deviations. Conservatively, we want to be able to detect a 0.35 SD or greater difference between any two groups with 5% significance and 80% power. For this, we need 129 children in each group, but to allow for 10% loss to follow-up, we will include 150 children in each group. However, given the factorial design, if there are no interactions between the two experimental interventions, we will be able to compare two groups of 300 children each, which will enable us to detect a difference as small as 0.24 SD. In the Treatfood trial, the SD of knee‐heel length at baseline was 18.1 mm [17]. Hence, a 0.24 SD difference corresponds to 4.3 mm. In secondary analysis, we will compare the 600 supplemented children with 150 unsupplemented. These group sizes will allow us to detect a 0.27 SD difference, corresponding to 4.9 mm.

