# Schedule of measurements and assessment

**
[figure not shown]
**

**
[figure not shown]
Figure 4: MAGMAM data collection time-points and visits.**

Timeline for enrolment, interventions, assessments and visits for each participant enrolled in the study. Phone follow-up and home visits are unfixed time points depending on need and availability. Time points are considered valid if taken within ±7 days of baseline, week 2 and week 4 and ±14 days from all other time points.

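### Children who pass 24 months during follow-up switch from lying to standing measurement, which costs the length/height primary outcome a little precision and is cheap to prevent

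*Protocol*

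**What the plan says.** Section 22 of the protocol (Child anthropometry) sets the measuring position by age: "Height (measured in children 24 months and older) and length (measured in children <24 months". The same paragraph gives the visits: "The following anthropometrics are taken at baseline, week 2, 4, 8 and 12 weeks". Section 11 admits children "Aged 12 - 59 months", so the 24-month cut lies inside the enrolled age range.

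The quantity affected is one of two primary outcomes. The Summary of protocol has "Primary outcome: Knee-heel length (mm) and total length (cm) over 12 weeks", and section 17 lists the second one as "Length/height velocity(cm". Section 17 adds: "All outcomes are measured over time from baseline to 12 weeks".

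The protocol does not say that a child keeps the baseline position, is measured both ways at the changeover, or has one measure converted to the other. Section 25 specifies longitudinal analysis and defers detail to a statistical analysis plan that is not at hand.

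**The concern.** Standing height is systematically shorter than lying length. A child measured lying at baseline and standing at week 12 therefore shows a change in cm equal to true growth minus the gap between the two positions. The step comes from the measuring method. Over only 12 weeks it can be a sizeable part of what one child gains.

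At stake are the precision of the milk protein isolate (MPI) and whey permeate (WP) comparisons on length/height, and the accuracy of the absolute growth reported. The rule also works against the protocol's own aim, stated under Anthropometrics in section 22, of limiting measurement variation by keeping staff and equipment constant.

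**Working it through.** **The plan's own figures.** The protocol gives no figure for the position switch, so the sample size is checked first. Section 18 states "we want to be able to detect a 0.35 SD or greater difference between any two groups with 5% significance and 80% power". With z-values 1.96 and 0.84, n = 2 × (1.96 + 0.84)² / 0.35² = 128.1, so 129 per group, as stated. Allowing 10% loss, 129/0.9 rounds up to 144, which the planned 150 covers. The factorial comparison with 270 v 270 remaining gives 2.80 × √(2/270) = 0.241 SD, matching the stated 0.24. The only SD in the protocol, 18.1 mm, is for baseline knee-heel length. None is given for length/height or its change.

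**Who switches.** Twelve weeks is 84/30.4375 = 2.76 months, so children aged 24 − 2.76 = 21.2 up to 23.9 months at inclusion cross the cut. Assume entry age is uniform over 48 months.

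- By week 12: p = 2.76/48 = 5.75%, or 750 × 0.0575 = about 43 children.
- Section 19 accepts visits within ± "14 days from all other time points". If every last visit fell at the late end, follow-up would be 98/30.4375 = 3.22 months, p = 6.7%, about 50 children.

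**Size in one child.** Assume a gap d of 0.5 to 1.0 cm and a true 12-week gain of 1.5 to 2.5 cm (neither is in the protocol). The step removes from 0.5/2.5 = 20% to 1.0/1.5 = 67% of that child's gain.

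**Size in the trial.** The overall mean change moves by −p × d. The added variance is p(1 − p)d², where p(1 − p) = 0.0575 × 0.9425 = 0.0542. The last three columns give variance inflation for an assumed SD of change of 1.0, 0.8 and 0.6 cm.

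| Gap d (cm) | Mean shift (cm) | Added variance (cm²) | SD 1.0 | SD 0.8 | SD 0.6 |
|---|---|---|---|---|---|
| 0.5 | −0.03 | 0.014 | 1.4% | 2.1% | 3.8% |
| 0.7 | −0.04 | 0.027 | 2.7% | 4.2% | 7.4% |
| 1.0 | −0.06 | 0.054 | 5.4% | 8.5% | 15% |

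**Power.** For week-12 change, 270 v 270 and a difference giving 80% power without the artefact, power becomes Φ(2.80/√(1 + inflation) − 1.96).

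- d = 0.7 and SD 1.0: 2.80/√1.027 − 1.96 = 0.80, power 79%.
- d = 0.7 and SD 0.8: about 78%.
- d = 1.0 and SD 0.8: about 77%.
- d = 1.0 and SD 0.6: 2.80/√1.15 − 1.96 = 0.65, power about 74%.

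**Between arms.** Crossing depends on age at entry, so the expected number of crossers is the same in each arm in proportion to its size. Chance imbalance adds a standard error of d × √(p(1 − p)) × √(2/270), about 0.01 to 0.02 cm for 270 v 270.

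**The case against.** The strongest reply is that this hardly touches the trial's question. The objective is the effect of MPI and WP, not absolute growth, and randomisation spreads the step evenly over the arms. Only one of two primary outcomes is involved. Knee-heel length is listed first, is the only outcome translated into mm in the sample size, and does not depend on the 24-month rule. All of this stands.

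Three stronger readings are tempting, and the documents do not support them:

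- A reader might infer that the step dilutes or biases the MPI and WP effects. Noise in a continuous outcome widens the standard error of a mean difference but does not shrink the difference, and crossing is unrelated to arm.
- A reader might infer bias in age subgroups. The protocol specifies no age-subgroup analysis, and within a baseline-age subgroup the arms are still randomised.
- A reader might take the 20% to 67% loss as the size of the problem. It describes about 6% of children one by one. The trial mean moves by 0.03 to 0.06 cm.

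The variance figures are also on the high side. The formula assumes that crossing children otherwise grow at the sample average. If they grow faster by δ, the added variance is p(1 − p)(d² − 2dδ), which is smaller. Fewer children have crossed by weeks 2, 4 and 8, and the analysis uses all visits.

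Finally, the wording could mean age at inclusion, and an anthropometry SOP or the statistical analysis plan, neither shown, might deal with the switch. Age at measurement is nonetheless the plain reading. A later conversion, or a covariate for position, can remove the average step but not the child-to-child differences in the gap. It also relies on knowing when the switch happened. Section 22 allows age to be established by questioning where no birth card exists, and nothing in the protocol says that position is recorded.

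**Conclusion.** The point holds as a matter of measurement precision. Followed as written, the age rule puts a position step into the raw cm change of about 5.8% of children, and nothing in the protocol prevents or corrects it. Under the assumed gaps and SDs, the cost is roughly 0 to 3 power points across mid-range values and about 6 at the extreme corner (gap 1.0 cm, SD 0.6 cm). Absolute growth is also slightly understated. The MPI and WP contrasts stay unbiased in expectation, and knee-heel length is unaffected.

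The size rests on uniform entry ages, the assumed gap and the assumed SD of change. It would grow if enrolment clustered just under 24 months: with 15% crossing and a 1.0 cm gap, power would be 73% to 78% for SDs of 0.8 to 1.5 cm. Severity is moderate to low. The reason to act is that prevention is nearly free and later repair only partial.

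**What to change.** In section 22 (Child anthropometry), state that each child keeps the baseline measuring position at weeks 2, 4, 8 and 12. Record the position on the CRF at every visit. Use these like-for-like values for the primary outcome in cm. For HAZ and WHZ, apply the length-height conversion whenever the position used does not match the child's age at that visit.

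The cost is one sentence in the protocol and SOP and one tick-box on the CRF. The downside is that some children just over 24 months are measured lying, and their z-scores need a conversion step. If data have already been collected under the age rule, the fallback is a stated conversion before change is computed, with a sensitivity analysis that leaves out the crossing children.
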